### Objective

The objective of the STITCH trial (Suture Techniques to reduce the Incidence of The inCisional Hernia) is to compare the small bites technique decribed by Millbourn et al. with a standardized large bites technique.

The overall objective of the study is reduction of the incidence of the most frequent complication of abdominal surgery, i.e., incisional hernia. We hypothesize that the small bites technique will result in a significant reduction of the incidence of incisional hernia, which may lead to a reduced morbidity and a better quality of life for patients and a significant reduction of costs.

Primary endpoint will be incisional hernia occurrence within one year after surgery, either clinically and/or ultrasonographically detected. Secondary endpoints include postoperative complications, in particular surgical site infection, burst abdomen and wound pain in the first postoperative month.

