### Outpatient clinic follow up

• Outpatient clinic visit at 1 and 12 months

○ Incisional hernia

○ Wound infection

○ Seroma formation

○ Other wound problems

○ Other abdominal wall hernia

• Ultrasound at 1 and 12 months

• VAS pain scores and Quality of Life forms preoperatively (day of operation or the day before) and at 1,3, 6 and 12 months

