#### Ultrasound examinations

During the 1 month and 1 year follow up an ultra sound examination will be performed to measure the distance between the rectus muscles at 3 point in the incision and check for incisional hernia. A specific score is used for the ultrasound examination. At ten points, which include 4 measurements of the distance between the rectus muscle, the quality of the scar in the abdominal wall is objectified. With this method the conclusion if there is an incisional hernia can also be made on the score list. In this list is controlled for:

An intact linea alba?

Bulging without Valsalva manouvre?

Bulging with Valsalva manouvre?

Distance between rectus muscles in scar on 1/3 cranial part in cm?

Distance between rectus muscles in scar on 1/3 caudal part in cm?

Maximum distance between rectus muscles in scar in cm?

Maximum distance between rectus muscles at place of bulging or defect in cm?

Is there a defect? If yes, the size of the defect and location

Is there fatty tissue in the defect?

Is there a bowel loop in the defect?

The radiologist is asked to make prints of every measurement and finding.

Quality of life will be assessed based on standardized Quality of Life forms including the EuroQol-5D and Short Form-36 before and at 1 month, 3 months, 6 months, and 12 months after surgery.

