### Sample size calculation

Millbourn et al. found a decrease in the incidence of incisional hernia from 18% to 5,6% in a randomized controlled trial [34]. In this trial, follow-up consisted of clinical instead of radiological examination for incisional hernia occurrence. In this trial, ultrasound examination will be used in order to be able to diagnose incisional hernia with higher sensitivity. It is expected that a relative decrease of the incidence incisional hernia after one year of 50% is reasonable. The mean reported one year incidence of incisional hernia in literature is 15%[1-5]. In order to reduce the mean incidence of incisional hernia from 15 to 7.5%, power calculations showed that two groups of 259 evaluable patients each are needed (power = 0.80, alfa = 0.05). Loss to follow-up is estimated at 10% of included patients. A total of 576 patients (2 × 288) will be included in the study to correct for loss to follow-up. Overall effects will be calculated adjusted for predictive baseline characteristics, which will lead to a higher statistical power.

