### Statistical analysis

Descriptive statistics will include median and interquartile range for continuous variables, and absolute numbers (with %) for categorical variables. Randomized groups will be compared for imbalance without formal statistical testing. Analysis will be by intention-to-treat. Differences between randomized groups will be tested with appropriate statistical methods, including t-tests or Mann-Whitney tests for continuous variables (considering whether the normality assumption is rejected by the Kolmogorov-Smirnov test with Lilliefors correction test), and chi-square tests for categorical variables. The primary outcome (incisional hernia) will be analyzed with Kaplan-Meier analysis and a Cox regression analysis, to adjust for any loss to follow up between 30 days and 1 year after surgery. The primary analysis is a covariate adjusted Cox model, which includes the following predefined, well-establihed predictors of incisional hernia: abdominal aneurysm aorta (AAA), obesity, diabetes, corticosteroid usage, radiotherapy, COPD, smoking, age, cancer, inguinal hernia, cardiovascular disease and collagen disorders.

Subgroup effects will be assessed by tests of interaction to prevent overinterpretation of apparent differences in effectiveness. Quality of life data will be analyzed by paired T-tests, comparing baseline with follow-up measurements, and repeated measures analysis. A two-sided p < 0.05 will be taken to indicate statistical significance.

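### The only quality-of-life comparison spelled out is follow-up against baseline; the protocol does not say which analysis gives the difference between small and large bites

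*Protocol article*

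**What the plan says.** The Objective section expects small bites to reduce incisional hernia, "which may lead to a reduced morbidity and a better quality of life for patients". Quality of life is listed under Secondary outcome. The instruments and times are given under Ultrasound examinations as "EuroQol-5D and Short Form-36 before and at 1 month, 3 months, 6 months, and 12 months after surgery", and the Outpatient clinic follow up section gives the same schedule.

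The Statistical analysis section has three statements that bear on the point:

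- specific to quality of life: "Quality of life data will be analyzed by paired T-tests, comparing baseline with follow-up measurements, and repeated measures analysis";
- general: "Differences between randomized groups will be tested with appropriate statistical methods, including t-tests or Mann-Whitney tests for continuous variables";
- threshold: "A two-sided p < 0.05 will be taken to indicate statistical significance".

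The repeated measures analysis is named without an arm effect, an arm-by-visit effect or a visit of interest. Nothing marks the paired tests as descriptive.

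**The concern.** A paired t-test against the preoperative score asks whether patients differ from how they were before surgery. Run on both arms pooled, it has no treatment term. Run in each arm, it gives two statements about recovery, and significance in one arm but not the other is not evidence that the arms differ. The same section already guards against this kind of error for subgroups by requiring interaction tests.

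Three routes are therefore open for one secondary outcome, all at the same threshold: paired tests, general two-group tests and a repeated measures model. They can give different answers, and no order of precedence is stated. The paired test is the only one described specifically for quality of life, so a reader could take its result as the trial's quality-of-life conclusion.

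**Working it through.** **Inputs.** The documents give no standard deviation, effect size or correlation for quality of life. The check takes 259 evaluable patients per arm from the Sample size calculation section and two-sided 0.05 from the Statistical analysis section. It assumes a standard deviation of 1 at each visit and a baseline/follow-up correlation r of 0.5 (0.3 to 0.7 for the variance factors).

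**The plan's own figure.** The section starts from "In order to reduce the mean incidence of incisional hernia from 15 to 7.5" per cent and states "two groups of 259 evaluable patients each are needed (power = 0.80, alfa = 0.05". For a time-to-event comparison, HR = ln(0.925)/ln(0.85) = 0.480. Required events are (1.960 + 0.842)² / (0.25 × ln(0.480)²) = 58.2. Then 58.2 / 0.1125 / 2 = 258.6, so 259 per arm, and 259/0.90 gives 288. The figure reproduces. It concerns hernia, and is used here only as the number of patients.

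**Step 1: two per-arm paired tests, equal true change in both arms.** The change score has SD √(2(1−r)) = 1 at r = 0.5. For a common change d, the power of each test is p ≈ Φ(d√259 − 1.96) for d > 0, and p = 0.05 at d = 0. The chance that exactly one arm is significant is 2p(1−p). The simulation used 4,000 runs per row.

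| Common change (SD) | p per arm | 2p(1−p) | Simulated disagreement |
|---|---|---|---|
| 0 | 0.05 | 9.5% | 9.2% |
| 0.125 | 0.52 | 49.9% | 49.0% |
| 0.175 | 0.80 | 31.5% | 31.4% |
| 0.2 | 0.90 | 19% | not run |
| 0.3 | 0.998 | 0.4% | 0.4% |

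The expression 2p(1−p) cannot exceed 50%, which it reaches at p = 0.5. The upper end is therefore the worst case, not an expected rate.

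**Step 2: a true arm difference of 0.25 SD.** With changes of 0.55 and 0.30 SD, both paired tests are significant in nearly every run and disagree in 0.2%. With changes of 0.25 and 0 SD, the same true difference, they disagree in 92.5%. Disagreement thus depends on how much both arms change, not only on how far apart they are. In the same two settings a between-arm t-test on change has power 0.82 and 0.80, and a baseline-adjusted between-arm comparison 0.91 and 0.90. In the runs with equal change, these two methods reject in 4.8% to 5.8% and 4.4% to 5.0%.

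**Step 3: one pooled paired test.** With equal change of 0.125 SD in both arms it is significant in 81% of runs, and in 98% to 100% at 0.175 SD or more. It detects change after surgery and carries no information on technique.

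**Step 4: what baseline adjustment gains.** With n per arm, the variance of the arm difference is:

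- follow-up only: 2σ²/n;
- change score: 2(1−r) × 2σ²/n;
- baseline-adjusted: (1−r²) × 2σ²/n.

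The adjusted variance is 1−r² of the first and (1−r²)/(2(1−r)) = (1+r)/2 of the second.

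| r | Reduction against follow-up only | Reduction against change score |
|---|---|---|
| 0.3 | 9% | 35% |
| 0.5 | 25% | 25% |
| 0.7 | 49% | 15% |

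**The case against.** The strongest reply is that a between-arm comparison is already available. Repeated measures analysis with two arms and five time points can carry an arm or arm-by-visit effect. The general rule for continuous variables compares randomised groups and does not exclude quality of life. The Economic evaluation section also plans a cost per QALY from the EQ-5D, within a ratio of differences between techniques. The article condenses a fuller plan, so model terms may properly sit elsewhere.

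Much of this stands, and it rules out several stronger readings:

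- A reader might infer that the plan cannot show an arm difference in quality of life. It can, by either of the routes just named.
- A reader might infer that per-arm p-values will be compared. The text does not say that the paired tests are run by arm, so Step 1 shows what would follow if they were.
- A reader might infer that the baseline goes unused. The paired test uses it, and the repeated measures model may.
- A reader might infer that VAS pain has no rule. The general between-group rule can cover it.

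The objection does not remove the stated test. A fuller plan could add terms to the repeated measures model, but a paired t-test would still not estimate the randomised contrast, and the article names it as an analysis without calling it descriptive.

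**Conclusion.** The point holds as a matter of aim and precedence. The one quality-of-life comparison that the article describes measures change after surgery. The analyses that could give the difference between techniques are not identified as doing so, and none is put first.

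The size depends on assumptions. Misleading disagreement between per-arm paired tests would run from about 9% at no common change, through a peak near 50% at a small one, to under 1% at a large one, and only if such tests were compared. The gain from baseline adjustment rests on the assumed correlation of 0.3 to 0.7. The outcome is secondary, and neither the sample size nor the primary analysis is affected. The change is still worth making, because it replaces a wrongly aimed test with one that answers the trial's question from data already planned.

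**What to change.** State in the Statistical analysis section that the inference for the EQ-5D and SF-36 is the between-arm difference, with confidence interval, at 1, 3, 6 and 12 months from the repeated measures model, adjusted for the baseline score. Preferably also include the randomisation factors, centre and operator type (surgeon or resident). State that this result takes precedence over the general two-group tests for these scales, and that paired changes from baseline are descriptive, without p-values.

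A between-arm test on change scores would also be valid, but is less precise under the assumptions above. The cost is one or two sentences of analysis wording, with no new data, visits or patients.

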#### Monitoring

The Erasmus University Medical center is the sponsor of this trial. Adverse events are defined as any undesirable experience occurring to a subject during a clinical trial, whether or not considered related to the investigational intervention. All adverse events reported spontaneously by the subject or observed by the investigator or his staff will be recorded. A serious adverse event (SAE) is any untoward medical occurrence or effect that at any dose results in death; is life threatening (at the time of the event); requires hospitalization or prolongation of existing inpatients' hospitalization; results in persistent or significant disability or incapacity; is a new event of the trial likely to affect the safety of the subjects, such as an unexpected outcome of an adverse reaction, major safety finding from a newly completed animal study, etc. All SAEs will be reported to the accredited Medical Ethical Committee (MEC) that approved the protocol, according to the requirements of that MEC. Serious Adverse events are death and burst abdomen. Adverse Events are readmission and reoperations.

An independent data and safety monitoring committee will evaluate the progress of the trial and will examine safety parameters every 3 months. The committee can unblind the data whenever deemed necessary based on reported adverse events. All involved physicians will repetitively be asked to report any potential adverse events caused by the study protocol. These adverse events will be listed and discussed with the monitoring committee. The monitoring committee can ask for a full report in order to discuss a specific adverse event. A copy of this report will be sent to the central ethics board and to the involved physicians. All deceased patients will be evaluated by the safety committee for cause of death and possible trial related serious adverse effects. Every death will be reported to the central ethics board and the local ethics board. The Data Safety Monitoring Board will consist of an epidemiologist/statistician and two independent surgeons.

#### Ethics

This study will be conducted in accordance with the principles of the Declaration of Helsinki and 'good clinical practice' guidelines. The Medical Ethical Committee of the Erasmus University Medical Center Rotterdam has approved the protocol. The Ethical Committees of the participating centers are applied for local feasibility. Prior to randomization, written informed consent will be obtained from all patients.

## Discussion

A major issue in all suture studies is standardisation of technique. In a multicenter trial it is difficult to achieve standardisation because many surgeons and residents will contribute in this trial. The benefit of a large group of participants is that the results will be representable for daily practice.

In this trial two major parameters have been standardized: the difference between small and large bites and the amount of stitches per running cm of wound resulting in an appropriate SL:WL ratio.

In daily practice, most surgeons use the large bite technique with large suture distances. With large bites, SL:WL ratio depends on the thickness of the abdominal wall including the muscles, the bite size, the number of stitches and the traction on the sutures during suturing. With large bites there is an unanswered question under which conditions an optimal SL:WL ratio of 4 should be reachable. With low traction on the suture fewer stitches are needed, but the slacking effect during the postoperative period will influence the results. For this reason in a RCT on suture techniques it is necessary to standardize the amount of stitches per centimetre of wound length.

## Conclusion

The STITCH trial is a multicenter randomized trial (trialregister: http://clinicaltrials.gov/ct2/show/NCT01132209) comparing the costs and effectiveness of a standardized small tissue bites suture technique with a standardized large tissue bites technique in midline incisions. This trial will provide the surgical society the evidence needed to optimize a surgical technique used to prevent common surgical complications.

## Appendix 1

### Criteria for defining a Surgical Site Infection (SSI)

#### Superficial Incisional SSI

Infection occurs within 30 days after the operation and infection involves only skin or subcutaneous tissue of the incision and at least one of the following:

1. Purulent drainage, with or without laboratory confirmation, from the superficial incision.

2. Organisms isolated from an aseptically obtained culture of fluid or tissue from the superficial incision.

3. At least one of the following signs or symptoms of infection: pain or tenderness, localized swelling, redness or heat and superficial incision is deliberately opened by surgeon, unless incision is culture-negative.

4. Diagnosis of superficial incisional SSI by the surgeon or attending physician.

Do not report the following conditions as SSI:

1. Stitch abscess (minimal inflammation and discharge confined to the points of suture penetration).

2. Incisional SSI that extends into the fascial and muscle layers (see deep incisional SSI).

### Deep Incisional SSI

Infection occurs within 30 days after the operation if no implant is left in place or within 1 year if implant is in place and the infection appears to be related to the operation and

infection involves deep soft tissue (e.g., fascial and muscle tissue) of the incision and at least one of the following:

1. Purulent drainage from the deep incision but not from the organ/space component of the surgical site.

2. A deep incision spontaneously dehisces or is deliberately opened by a surgeon when the patient has at least one of the following signs or symptoms: fever (> 38°C), localized pain, or tenderness, unless site is culture negative.

3. An abscess or other evidence of infection involving the deep incision is found on direct examination, during re-operation, or by histopathological or radiological examination.

4. Diagnosis of a deep incisional SSI by a surgeon or attending physician.

#### Notes

1. Report infection that involves both superficial and deep incision sites as deep incisional SSI.

2. Report an organ/space SSI that drains through the incision as a deep incisional SSI.

### Organ/Space SSI

Infection occurs within 30 days after the operation if no implant is left in place or within 1 year if implant is in place and the infection appears to be related to the operation and infection involves any part of the anatomy (e.g., organs or spaces), other than the incision, which was opened or manipulated during an operation and at least one of the following:

1. Purulent drainage from drain that is placed through a stab wound into the organ/space.

2. Organisms isolated from an aseptically obtained culture of fluid or tissue in the organ space.

3. An abscess or other evidence of infection involving the organ/space that is found on direct examination, during reoperation, or by histopathologic or radiologic examination.

4. Diagnosis of a deep organ/space SSI by a surgeon or attending physician.
